#### Analysis of secondary outcomes

The secondary objectives will be analyzed based on the nature of the variable under evaluation. Parametric tests, such as Student’s t-test, or non-parametric tests, such as the Wilcoxon-Mann-Whitney test for independent data, will be employed for secondary analyses comparing the two treatments, depending on the normality or non-normality of the quantitative data distribution. For categorical variables, the Chi-square test or Fisher’s exact test, as appropriate, will be used.

Secondary analyses will be conducted in the intention-to-treat (ITT) analysis population.

Given that randomization has been carried out with oocyte donors rather than recipients, caution must be exercised when interpreting the results for the latter. To mitigate potential biases and control for the possibility of a single donor contributing oocytes to multiple recipients, the impact of different treatments will be assessed using a multilevel analysis. This analysis will consider the hierarchical or nested structure of our data and will be multivariable, incorporating various covariates to control for potential biases.

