## Outcomes

The primary objective of this study is to compare the efficacy (non-inferiority) of the MNP protocol (Seidigestan®) to an antagonist protocol, using the number of mature metaphase II (MII) oocytes as the primary outcome variable.

Our secondary objectives are detailed in **Table 1**.

**Table 1 T1:** Secondary outcomes for comparison of oral progesterone vs GnRH antagonist.

Treatment	Analyzing and comparing the baseline characteristics of each group of donors
	Comparing the gonadotrophin dose and treatment duration
Laboratory	Fertilization rate per-oocyte injected
	Assessing whether there are differences in the performance of these MII oocytes in fresh cycles and their potential to develop into blastocysts after ICSI
Clinical	Documenting the fresh transfers of blastocysts originating from each protocol and the endometrial preparation protocols
	Biochemical pregnancy: a pregnancy diagnosed only by the detection of beta hCG in serum or urine, which fails to progress to the point of ultrasound confirmation
	Clinical pregnancy: an intrauterine pregnancy diagnosed by ultrasonography
	Ongoing pregnancy: the presence of a heartbeat as seen by ultrasonography 12 weeks gestation
	Multiple pregnancy: two or more gestational sacs seen by ultrasonography
	Early pregnancy loss: the spontaneous loss of an intrauterine pregnancy, where there is no fetal heartbeat detected at the time of ultrasound at 6–8 weeks
	Ectopic pregnancy: a pregnancy outside the uterine cavity, diagnosed by ultrasound, surgical visualization or histopathology
	Miscarriage: the spontaneous loss of an intrauterine pregnancy with fetal heartbeat prior to 20 completed weeks of gestational age
	Live birth: the complete expulsion or extraction from a woman of a product of fertilization, after 22 completed weeks of gestational age; which, after such separation, breathes or shows any other evidence of life, such as heartbeat, umbilical cord pulsation or definite movement of voluntary muscles, irrespective of whether the umbilical cord has been cut or the placenta is attached
	Analyzing possible obstetric differences between both protocols
Cost-effectiveness	Contrasting the economic cost per number of mature oocytes (MII) obtained in each treatment regimen
Quality of life	Women will also be asked to complete a survey consisting of questions related to treatment tolerability

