#### Data analysis

The descriptive statistical methods employed in this study will depend on the nature of the analyzed variables. For qualitative variables, the following descriptive statistics will be computed: frequency and percentage. Quantitative variables will be presented using measures of central tendency and dispersion.

For univariate statistical analysis of qualitative variables, the Chi-square test or Fisher’s exact test will be utilized. Normality of quantitative variables will be assessed through the Kolmogorov-Smirnov and Shapiro-Wilk tests, as well as visual examination of distribution (histogram, QQ-plot, and box plot). If the distribution is found to deviate from normality, logarithmic transformation of the variable will be applied. Subsequently, univariate analysis of quantitative variables will be performed using the t-Student test. Statistical significance will be considered at P < 0.05, and conclusions will be drawn with support from confidence intervals whenever applicable.

The primary objective of the study will be analyzed through an ANCOVA, using the treatment group assignment as a covariate, to determine whether there is an equivalent effect among subgroups or not.

For the analysis of secondary objectives, a multilevel model will be employed, considering the hierarchical structure of the data due to the fact that one donor may contribute to multiple recipients, as well as the number of cycles.

Data will be entered into a database within our department and analyzed using statistical software packages SPSS version 22.0 for Windows (SPSS Inc., Chicago, IL) and R version 4.2.2 for Windows (R Foundation for Statistical Computing, Vienna, Austria).

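### Secondary outcomes are given both independent-data tests and a multilevel model with no rule for which governs, and the unit of analysis for per-oocyte outcomes is not fixed

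*Protocol article*

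**What the plan says.** The Data analysis section of the protocol article states: "For the analysis of secondary objectives, a multilevel model will be employed". The reason given is that "one donor may contribute to multiple recipients, as well as the number of cycles" create a hierarchy. The sentence is not limited to recipient outcomes.

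The section Analysis of secondary outcomes chooses tests by type of variable. For quantitative variables, Student's t-test or "non-parametric tests, such as the Wilcoxon-Mann-Whitney test for independent data, will be employed for secondary analyses comparing the two treatments", depending on normality. For the rest: "For categorical variables, the Chi-square test or Fisher’s exact test, as appropriate, will be used". A later paragraph of the same section adds a multivariable multilevel analysis, meant to "control for the possibility of a single donor contributing oocytes to multiple recipients", and says: "This analysis will consider the hierarchical or nested structure of our data". The levels are not listed.

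Table 1 (Outcomes) includes two laboratory outcomes that arise oocyte by oocyte: "Fertilization rate per-oocyte injected", and the development of MII oocytes into blastocysts. It also lists recipient outcomes such as clinical and ongoing pregnancy. The article states that donors, not recipients, were randomised.

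**The concern.** There are two linked problems.

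First, the same outcome can fall under two methods. Clinical pregnancy is categorical, so the variable-type rule sends it to Chi-square or Fisher's test. The Data analysis section and the closing paragraph on secondary outcomes send it to a multilevel model. Neither result is named as decisive, so the choice could be made after both are known.

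Second, the clustering that is spelled out is the weaker one. At a minimum of 8 MII oocytes per recipient, a donor serves fewer than two recipients on average, but she contributes about 13 or 14 oocytes. Whether an oocyte fertilises is a yes/no variable, and the only rule stated for categorical variables is Chi-square or Fisher's test. On pooled oocytes, either test would treat about a thousand oocytes per arm as independent when 75 donors per arm were randomised. Confidence intervals would then be too narrow, and chance differences between the protocols in oocyte performance would be declared significant too often.

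**Working it through.** **The plan's own figure.** The article gives no intra-donor correlation, design effect or sample size for any secondary outcome. Its only sample size is for the primary outcome: SD 6.997, difference 3, one-sided alpha 0.05, power 80%. Then n per arm = 2 × (1.645 + 0.842)² × 6.997² / 3² = 67.3, rounded up to 68, or 136 in total, as stated. Adding 10% gives 136 × 1.1 = 149.6, so 150. (Dividing by 0.9 gives 152, a trivial difference.) This calculation has one value per donor, so the present point does not touch it.

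**Inputs for the per-oocyte check.**
- Oocytes per donor: mean m = 13.58, SD 6.997 (Sample size section), so CV = 6.997 / 13.58 = 0.515.
- Donors per arm: 75, so 75 × 13.58 = 1,018 oocytes per arm.
- Intra-donor correlation (ICC): not in the article. It is assumed here, over the range 0.01 to 0.20.

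**Formulas.** With unequal cluster sizes, DE = 1 + [(1 + CV²) × m − 1] × ICC. Here (1 + 0.515²) × 13.58 = 17.19, so DE = 1 + 16.19 × ICC. The true two-sided error of a nominal 5% test that ignores clustering is 2 × [1 − Φ(1.96 / √DE)]. For example, at ICC 0.05, DE = 1.81, 1.96 / √1.81 = 1.457, and the error is 14.5%.

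| Assumed ICC | DE | True error, formula | True error, simulation | Effective oocytes per arm |
|---|---|---|---|---|
| 0.01 | 1.16 | 6.9% | not run | 877 |
| 0.02 | 1.32 | 8.8% | 8.6% | 769 |
| 0.05 | 1.81 | 14.5% | 14.8% | 563 |
| 0.10 | 2.62 | 22.6% | 22.7% | 389 |
| 0.20 | 4.24 | 34.1% | 33.8% | 240 |

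The simulation drew beta-binomial outcomes for 75 donors per arm, with an assumed event rate of 0.75 and 4,000 runs per ICC. With ICC 0 the pooled test gave 4.8%, as it should. If every donor had exactly 13.58 oocytes, the formula would give 12.5%, 19.2% and 29.6% at ICC 0.05, 0.10 and 0.20. If fewer oocytes are injected than 13.58 per donor, the inflation is smaller.

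**One rate per donor.** In the same simulations (ICC 0 and 0.02 to 0.20), comparing each donor's own rate between arms gave 4.6% to 5.4% error for the t-test and 4.8% to 5.2% for the Wilcoxon test. These tests are sound when the donor is the unit.

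**Recipient outcomes.** 13.58 / 8 = 1.7 recipients per donor. With DE = 1 + 0.7 × ICC, the design effect is 1.035, 1.07 and 1.14 at ICC 0.05, 0.10 and 0.20, and the error of a test that ignores clustering is 5.4%, 5.8% and 6.6%.

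**The case against.** A reader might infer that the laboratory p-values will be far too small. The article does not support that. It nowhere says that oocytes will be pooled. A donor's fertilisation rate is itself a quantitative variable, so the variable-type rule could equally send it to the t-test or Wilcoxon test, which are valid on one value per donor. The t/Wilcoxon sentence is therefore not at fault. The risk lies in the Chi-square/Fisher sentence, and only if it is applied to oocytes. This part of the objection stands, and it makes the inflation conditional.

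Nor are oocytes clearly excluded from the multilevel model. The wording about a nested structure is general, the Data analysis section covers all secondary objectives, and a donor random effect would handle correlation among oocytes from one donor. What remains is that the only structure the article explains is a donor serving several recipients, plus a number of cycles.

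The two sets of methods could also be a sequence (simple tests first, then a multivariable model, as for the primary outcome) or a division (simple tests for donor outcomes, multilevel for recipients). Either would be reasonable, but the article states neither, and the unrestricted sentence in Data analysis conflicts with the division. An outcome-by-outcome table may well be left to an analysis plan that is not shown. Overlapping assignments in the text that is shown are a different matter.

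Finally, it would go too far to say that the laboratory results are meant to prove equal oocyte performance. Table 1 speaks of assessing differences and the Discussion of exploring them.

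**Conclusion.** The point holds in a limited form. The article assigns independent-data tests and a multilevel model to the same secondary objectives without saying which decides. It also leaves open whether fertilisation and blastocyst development are analysed by oocyte or by donor.

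The size depends on two things the article does not settle: whether oocytes are pooled, and the intra-donor correlation. If they are pooled, a nominal 5% test has a true error of about 7% to 9% at ICC 0.01 to 0.02, 15% at 0.05, 23% at 0.10 and 34% at 0.20. If each donor contributes one rate, there is no inflation. For recipient outcomes the effect of ignoring clustering is small, and the main issue there is the unresolved choice between methods. The primary outcome has one value per donor and is unaffected. The correction is worth making before analysis, but it does not threaten the trial's main conclusion.

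**What to change.** Name one decisive analysis for each secondary outcome:

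- **Fertilisation and blastocyst development:** either one rate per donor, compared by t-test or Wilcoxon test, or a mixed-effects logistic model or GEE with donor as the cluster (recipient within donor where applicable). The first weights every donor equally and the second does not, so choose in advance. State that Chi-square or Fisher's test will not be applied to pooled oocytes.
- **Pregnancy outcomes:** make the multilevel model with recipients within donor decisive, in place of Chi-square or Fisher's test.
- **Outcomes with one value per donor** (gonadotropin dose, duration, tolerability): keep the simple independent-data tests.

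The cost is a change of wording, slightly more analysis work, and wider intervals than a pooled test would show. The sample size does not change.

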Ovarian stimulation will be discontinued in the event of poor response (*i.e.* ≤ 8 follicles ≥ 14 mm), and consequently, the administration of any medication will cease if the criteria for final oocyte maturation are not met within a maximum of 14 days from the initial gonadotropin dose administration.

The final visit will involve a telephone call conducted 72 hours after the oocyte retrieval to gather information regarding any surgical or stimulation-related complications.

Our donor program ensures a minimum of 8 metaphase II oocytes per recipient. Therefore, cumulus-corona-oocyte complexes (CCOs) are decumulated on the day of the donor’s oocyte retrieval and fertilized using intracytoplasmic sperm injection (ICSI). Only in exceptional cases, as determined by medical judgment, where conventional IVF may be more beneficial, will the decumulation process not be performed. All embryo transfers will occur at the blastocyst stage.

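### The ITT label on all secondary analyses cannot cover per-recipient outcomes, because which randomised donors contribute recipients, and how many, depends on oocyte yield

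*Protocol article*

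**What the plan says.** The Protocol article, Analysis of secondary outcomes, assigns one analysis set to everything secondary: "Secondary analyses will be conducted in the intention-to-treat (ITT) analysis population". No exception is made for recipients. Table 1 under Outcomes lists donor-level items (gonadotropin dose, treatment duration, cost per mature oocyte) together with recipient-level items (pregnancy endpoints, miscarriage, live birth). The clinical items begin with "Documenting the fresh transfers of blastocysts originating from each protocol and the endometrial preparation protocols".

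The same analysis section concedes that recipients were not the randomised unit: "Given that randomization has been carried out with oocyte donors rather than recipients, caution must be exercised when interpreting the results for the latter". Its remedy is that "the impact of different treatments will be assessed using a multilevel analysis", a model that "will be multivariable, incorporating various covariates to control for potential biases". Data analysis gives the reason for the multilevel structure: "one donor may contribute to multiple recipients, as well as the number of cycles".

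Two statements under Oocyte donors and ovarian stimulation determine who can supply a recipient: "Ovarian stimulation will be discontinued in the event of poor response" and "Our donor program ensures a minimum of 8 metaphase II oocytes per recipient".

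**The concern.** An ITT comparison keeps every randomised unit in the arm to which it was assigned. Here that unit is the donor, and a per-recipient analysis has no row for a donor who supplied nobody. The number of rows for the other donors rises with their yield. Yield is measured after randomisation and is the primary outcome, so the trial itself treats it as something the progesterone protocol might change.

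The planned remedies address other problems. A donor-level random effect allows for correlation between recipients of the same donor. Covariates address differences in recipient mix. Neither brings back a donor with no recipient, nor shows that one arm served fewer recipients.

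What is at stake is how the recipient result will be read. The Discussion counts the ability to examine ongoing pregnancy among the trial's strengths, and cites an earlier donor trial in which ongoing pregnancy was 26.7% with MPA against 39.9% without, although mature oocyte numbers were comparable. Readers will look for this result. Under an ITT label, equal per-recipient rates could be taken to mean that the arms perform equally for each donor randomised, which does not follow if yields differ.

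**Working it through.** **The plan's own figure.** The only stated sample size is for the primary outcome. With a difference of 3, SD 6.997, one-sided alpha 0.05 and 80% power, n per arm = 2 × [(1.645 + 0.842) × 6.997 / 3]² = 67.3, which rounds up to 68, or 136 in total. This matches the plan. It has no bearing on recipient outcomes, for which no figure is given.

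**Inputs from the article.** Control mean 13.58 and SD 6.997, the 3-oocyte difference and 75 donors per arm (Sample size); a minimum of 8 MII per recipient (Oocyte donors and ovarian stimulation).

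**Assumptions that the article does not supply.**
- The planning mean and SD, given there for oocytes, apply to MII.
- Recipients per donor = floor(MII / 8), with no shortfall covered from elsewhere.
- MII follows a negative binomial distribution with the SD held at 6.997 as the mean μ falls, so the size parameter is k = μ² / (6.997² − μ). At μ = 13.58, k = 184.42 / (48.96 − 13.58) = 5.21.
- The pregnancy rate per recipient is 40% in both arms.

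**Results per randomised donor.**

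| Deficit in mean MII | Share with fewer than 8 MII | Recipients per donor | Ratio to no deficit | Pregnancies per donor (× 0.40) |
|---|---|---|---|---|
| 0 | 19% | 1.26 | 1.00 | 0.50 |
| 1 | 25% | 1.13 | 0.90 | 0.45 |
| 1.5 | 28% | 1.07 | 0.85 | 0.43 |
| 3 | 39% | 0.89 | 0.71 | 0.35 |

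Per 75 donors, about 15 supply no recipient with no deficit (75 × 0.195 = 14.6), and about 29 at a deficit of 3 (75 × 0.389 = 29.2).

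**Sensitivity to the distribution.** A rounded normal with the same mean and SD gives 19% below 8 MII with no deficit, 26% at 1.5 and 33% at 3. Recipients per donor are 1.28, 1.11 and 0.95, so the ratio at a deficit of 3 is 0.74 instead of 0.71.

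**Reading.** In every row the per-recipient comparison is 40% against 40%. The per-donor comparison ranges from no difference to about 29% fewer pregnancies (1 − 0.89 / 1.26). The ratio does not depend on the 40%, which cancels.

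**The case against.** The strongest reply is that the article already guards against the misreading. Directly after the ITT sentence it says that donors rather than recipients were randomised and asks for caution, and elsewhere it describes the recipient results as exploratory. The ITT sentence covers all secondary outcomes and is right for the donor-level ones. This stands in part. The caution is real, but the reasons given with it are shared donors and unspecified biases. Selection on yield is not named, and the ITT sentence is left unqualified.

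Second, the per-recipient rate answers a proper question: how mature oocytes perform once obtained. Quantity is already compared in all randomised donors through the primary outcome, and a per-donor pregnancy count mixes the two. This stands, and it is why the per-recipient analysis should be kept. A reader might infer from the illustration that the per-recipient rate is biased. That is not supported: the illustration assumes equal rates and the analysis reports them correctly. Bias would require the contributing donors to differ between arms in ways related to oocyte quality, and nothing in the article shows this.

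Third, the mechanism is partly inferred. A reader might take the 8-MII minimum as a strict gate, or conclude that recipients left without oocytes or a transfer are dropped. The article says neither. It does not state how a shortfall is handled or what the recipient denominator is, and an article may leave both to the full protocol or SAP. Donors whose stimulation is stopped supply no oocytes whatever the allocation rule, so the point about the label does not rest on the gate.

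Finally, a 3-oocyte deficit is the unfavourable end. At that true difference the planned test would declare non-inferiority only about 5% of the time, so readers would usually already know that yield was lower. The smaller deficits in the table are the fairer guide.

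**Conclusion.** The point holds in a limited form. The ITT label is wrong as written for per-recipient outcomes, because both the inclusion of a randomised donor and her weight depend on MII yield, and neither the multilevel model nor the caution about recipients deals with that. The label remains correct for donor-level secondary outcomes.

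The size is conditional. If yields are equal in the two arms, the gap per randomised donor is zero, although the label is still inaccurate. If the progesterone arm yields fewer MII, pregnancies per randomised donor would be about 10% lower at a deficit of 1 oocyte, 15% at 1.5 and 29% at 3, with equal per-recipient rates. These figures rest on the planning mean and SD applying to MII, one recipient per complete 8 MII without topping-up, and the negative binomial model. They illustrate what a per-recipient analysis cannot show. They do not estimate a bias in the per-recipient rate.

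**What to change.** In Analysis of secondary outcomes:

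- Restrict the ITT wording to donor-level secondary outcomes such as gonadotropin dose, treatment duration and cost.
- Keep the multilevel recipient analysis, but describe it as conditional on donation and exploratory.
- Report by assigned arm the number of randomised donors with no recipient, and the number of recipients per randomised donor.
- Add, as a supportive ITT analysis, ongoing pregnancies and live births per randomised donor, counted as zero where there is no recipient, with the difference or ratio between arms and its 95% CI.

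The cost is a few changed sentences and one extra table. No additional donors are needed. The outcomes are already planned, and the multilevel model already requires each recipient to be linked to her donor. The drawback is that the per-donor endpoint is noisier and mixes oocyte quantity with quality, which is why it should support the per-recipient analysis and not replace it.

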### Data management and monitoring

The data collected must be transcribed into the Data Collection Notebook (DCN), and this data will be considered as valid information for the subsequent evaluation of the efficacy and safety of the treatments under study. The DCNs should be completed accurately, and in cases where previously transcribed data need correction, they should be crossed out with the correct value noted beside them. Corrections must always be dated and validated by the signature of the principal investigator or their collaborators.

The documents pertaining to this trial will be archived by the investigator for up to five years following the completion of the clinical trial. In any case, a participant identification list will always be maintained. The sponsor, Instituto Bernabeu, will keep the primary study archive for a period of five years.

Monitoring of the study is expected to be conducted in accordance with the procedures outlined in the Standard Operating Procedure (SOP) of the monitoring and follow-up Unit of the institute.

The controlled ovarian hyperstimulation cycles of the oocyte donors will be monitored according to the center’s standard criteria.

Regarding the handling of personal data in the study, such data will be processed and safeguarded by qualified members of the medical team with the utmost confidentiality, in compliance with the prevailing data protection regulations, including Regulation (EU) 2016/679 of the European Parliament and of the Council of 27 April 2016 on the protection of natural persons with regard to the processing of personal data and on the free movement of such data (GDPR), and the Spanish Organic Law 3/2018 of 5 December on the Protection of Personal Data and the Guarantee of Digital Rights (LOPDGDD), as well as any other relevant regulations and legislation.

To safeguard the confidentiality of the subjects’ personal data, only the principal investigator, their collaborators, and the technical personnel involved in the study will have access to their identities but they will not be disclosed to sponsors. For the same reason, complete personal identification data and written consent will be stored in the investigator’s center archive. Information regarding the identity of the patients will be considered confidential for all purposes. Patient data collected in the CRD during the study will be documented in an anonymous and dissociated manner, linked to a code (patient number), so that only the investigator can associate such data with an identified or identifiable person. The database generated by the study will not contain any patient identification, only a numerical code that cannot be used to reveal their identity. The information collected in the study will always be treated as aggregated data and never as individual or personal data, thus maintaining anonymity and confidentiality.

